## Abstract

**Background:** Subclinical depression is a prevalent mental health problem and increases the incidence of the onset of major mood disorders, such as major depressive disorder (MDD). Psychological interventions have been proved to be effective for reducing depressive symptoms for people with subclinical depression and can prevent the onset of MDD. However, people have limited access to face-to-face psychotherapy. Internet-based psychological intervention is an alternative treatment option. The aim of the study is to evaluate the efficacy of MoodBox, an online psychological intervention program, for subclinical depression.

**Methods:** This study is a multicenter, randomized, controlled, non-blinded superiority study with three parallel groups. A total of 435 first-year university students with subclinical depression will be recruited. Eligible participants will be randomly assigned to the MoodBox group, the online psychoeducation group, and the naturalistic observation group at a ratio of 1:1:1. The intervention period is 8 weeks, and participants will be continuously followed up for 1 year. The primary outcome of the study is the efficacy of the intervention, defined as measured by the Patient Health Questionnaire (PHQ-9).

**Discussion:** This is the first study to innovatively develop and test an intervention to improve psychological well-being and decrease the incidence of MDD in a subclinical depression population in China. Once proven effective and acceptable, MoodBox could be potentially integrated into the routine clinical service to facilitate the management for people with subclinical depression.

**Clinical Trial Registration:** The trial is registered with the Chinese Clinical Trial Registry on 21 July 2020 (No. ChiCTR2000034826).

## Introduction

Subclinical depression, also known as subthreshold depression, subsyndromal depression, or minor depression, is considered to be a condition that does not meet the diagnostic criteria for depression but present with at least two and no more than four depressive symptoms, which must include one of the core symptoms of major depressive disorder (MDD) (i.e., depressed mood or anhedonia) and last a duration for at least 2 weeks (1–3). The prevalence of subclinical depression ranges from 1.3 to 17% in primary care and from 1.4 to 17.2% in community settings (2). Subclinical depression has detrimental effects on psychosocial function and quality of life, increases service utilization, and carries a high risk of developing into a full-blown depression (4, 5). Furthermore, a meta-analysis indicated that the mortality rates in subclinical depression are comparable with those in MDD (6).

Although depressive disorders are the most frequent consequence of subclinical depression, it can also lead to other mood disorders. From the clinical staging approach, subclinical depression could be the prodromal stage for a variety of mental health problems (7). However, studies on subclinical depression mostly focus on preventing the onset of depression, and other mood disorders are commonly overlooked (8, 9). Moreover, in light that depressive episode is usually the first episode of bipolar disorder (10), especially in young age, the reduction of depressive symptoms is not equivalent to remission of subclinical depression; alternatively, it may be a sign for the development of mania or hypomania. Therefore, a comprehensive assessment of mood events is necessary for subclinical depression.

Psychotherapy is effective in reducing depressive symptoms for people with subclinical depression and can prevent the onset of MDD (11). Although medication is recommended to treat depression, no evidence has supported the use of medication for subclinical depression (12). Cognitive behavioral therapy (CBT), interpersonal psychotherapy (IPT), problem-solving therapy (PST), and internet-based psychotherapy are primary choices for treating subclinical depression and preventing depression (13). However, traditional psychotherapy (i.e., face-to-face therapy carried out by a therapist) is not suitable for the preventive use in a large population, due to the limited number of qualified therapists and high costs (14–16). Moreover, in China, currently, mental health service is prioritized for people who meet the clinical threshold, and people with subclinical conditions are largely underserved (17).

Internet-based psychotherapy has the advantage of being accessible at any time and place, people can work in their own pace, and at-risk individuals can be reached more timely as compared with traditional face-to-face approach (18). Therefore, an effective internet-based psychological intervention has the potential to meet the need for the underserved population. Although internet-based interventions have been proved effective in western countries (18–20), to date, in China, no internet-based psychological intervention for subclinical depression has been developed and tested. To address the gap, informed by evidence-based psychological interventions for subclinical depression (e.g., CBT and IPT), we developed an internet-based psychological intervention program, named MoodBox, for people with subclinical depression, and we carried out a randomized controlled trial (RCT) to test the efficacy of the program. The primary aim of the study is to evaluate the efficacy of MoodBox for subclinical depression. The secondary aims are to evaluate the feasibility, usability, acceptability, and safety of MoodBox. To the authors' knowledge, MoodBox is the first internet-based intervention for subclinical depression in China.

## Methods

### Study Design

The study is a multicenter, randomized, controlled, non-blinded superiority study with three parallel groups. People with subclinical depression will be invited to participate in the study. Eligible participants will be randomly assigned to one of the three groups—the MoodBox group, the online psychoeducation group, and the naturalistic observation group—at a ratio of 1:1:1. By designing a three-arm study and choosing online psychoeducation and naturalistic observation as comparators, we aim to minimize the influence of digital placebo effect and the natural remission of subclinical depression. The intervention period of the study is 8 weeks. Following the completion of the intervention period, the participants will be continuously followed up for 1 year. All assessments will be conducted remotely using a social media app (WeChat) to send out notifications to participants. At each follow-up time window, a notification will be sent out via the WeChat public account to remind the participant to fill out a set of self-report scales. The participants will be asked to report general information, symptom severity, social functioning, childhood traumatic experiences, parenting experiences, attachment, and coping style at the baseline and to report their symptom severity and social functioning at each follow-up time point. After the baseline assessment, the participants will be assessed at 2, 4, and 6 weeks after they started to receive the intervention and a post-intervention assessment at 8 weeks. After that, participants will enter the follow-up phase and will be assessed at 12-week, 6-month, 9-month, and 12-month follow-up time points. See Figure 1 for a flowchart demonstrating the study procedure in detail. The study has been registered as a clinical trial on the Chinese Clinical Registry website (Registration number: ChiCTR2000034826).

**Figure 1 F1:**
[figure not shown]
Overview of the study design.

### Participation Eligibility

The eligibility of participants will be assessed in accordance with the following inclusion and exclusion criteria by psychiatrists through clinical interview and relative scales. The inclusion criteria are (1) age 18 years or older, no restriction for gender; (2) the score of two to four items on the Patient Health Questionnaire (PHQ-9) scale ≥ 2 (must include the first or second item, which are the indicator for core symptoms of depression) and a total score ≤ 9; (3) not meeting diagnostic criteria for any mental disorders according to the *Diagnostic and Statistical Manual of Mental Disorders* (Fourth Edition) (DSM-IV); and (4) being able to give consent. The exclusion criteria are (1) having severe and unstable physical illness; (2) having organic brain damage; or (3) being alcohol or drug dependent. A psychiatrist will be using Mini-International Neuropsychiatric Interview (MINI) to rule out any mental disorders. The exclusion criteria will be assessed through clinical interview by completing a screening checklist of the study.

### Sample Size

Four hundred thirty-five participants are intended to enroll and will be randomized with a ratio of 1:1:1. The estimated sample size provides 80% power (two sided α = 0.025, considering a multiple comparison) to detect difference in the primary outcome and the proportion of participants without subclinical depression between the MoodBox group with the online psychoeducation group and the observation group in a survival analysis (assuming the minimum difference is 14%) after 8 weeks. Taking into account a predicted 20% attrition for this comparison, at least 145 participants would be needed in each group. The calculation was based on a meta-analysis that reported clinical difference between the internet-based intervention group and psychoeducation group (9), and the calculating methods were in accordance with Chow et al.'s instruction (21).

### Recruitment and Randomization

The study is a multicenter, three-arm, parallel RCT. The study will be conducted at three universities in Beijing, China. First-year students who are waiting for the regular physical examination will be invited by research staff to complete a brief screening questionnaire to assess their eligibility. Students who meet the eligibility criteria will be provided with the participant information sheet and the consent form of the study. If the participants were interested in participating in the study, research staff would give a more comprehensive face-to-face explanation of the study in a private consultation room. Written consent will be required before the participant formally enrolls in the study. Eligible participants will be randomly assigned to three groups—the MoodBox group, the online psychoeducation group, or the observation group—with a ratio of 1:1:1. Randomization will take place after the completion of baseline assessment using a randomization code, which will be developed in SAS 9.4 (SAS Institute Inc., Cary, NC, USA) by a statistician who is not involved in the study.

### Intervention

#### MoodBox Group

The MoodBox group will receive an 8-week internet-based psychotherapy program. The program is a web-based psychological intervention informed by evidence-based psychological interventions, including CBT, IPT, and mindfulness meditation. The program consists of four core modules, which are symptom assessment, cognitive therapy, interpersonal therapy, and relaxation. There are 20 sessions in total, and each session takes approximately 30 min to complete. Participants are expected to complete a minimum of two sessions per week. After finishing each session, participants will receive a virtual trophy in the program as a reward. Participants will be assigned with a user account and receive training of the program at the first visit.

An outline of a brief description of the internet-based intervention program contents can be found in Table 1. The first module (session 1) of MoodBox is an introduction of the program that provides a comprehensive explanation of depression and the program, and there is an assessment of depression using PHQ-9 at the end of this session. The second module is cognitive intervention (sessions 2–11), which is based on cognitive reconstruction technique of CBT. This module will illustrate by animation the different types of automatic thoughts that are related to depression. After the illustration, participants will be required to identify their own automatic thoughts and to practice modifying the automatic thoughts by doing exercises in the program. The third module is interpersonal intervention (sessions 12–18). This module is based on IPT theory and focuses on interpersonal problems related to depression. The fourth module is relaxation, which includes mindfulness meditation and relaxation music. This module is not stand-alone; instead, it was embedded in other modules and would be presented after finishing each session. The final module is review and termination (sessions 19 and 20). In this module, participants will review all the previous sessions and will be given advice for their future life.

**Table 1 T1:** The content of the MoodBox program.

**Themes**	**Contents**	**Session**
Introduction	What is depression?	Session 1
	What is MoodBox?	Session 1
	Introduction of the process of MoodBox	Session 1
	Symptom assessment	Session 1
Cognitive intervention	Learning automatic thoughts	Sessions 2–6
	Identify distortion thoughts	Sessions 2–6
	Practicing cognitive intervention techniques	Sessions 7–10
	Review and testing	Session 11
Interpersonal intervention	Interpersonal problem diagnoses	Session 12
	Learning interpersonal theory	Session 13
	Practicing interpersonal intervention	Sessions 14–17
	Review and testing	Session 18
Relaxation	Mindfulness meditation	Sessions 2–10 and Sessions 12–17
	Relaxation music	Sessions 2–6
Review and termination		Sessions 19–20

#### Online Psychoeducation Group

For the online psychoeducation group, a psychoeducation website will be provided. The website will deliver psychoeducation that includes general information about depression and tips for managing depressive moods. However, the psychoeducation website does not contain any therapeutic contents. Participants will be asked to visit the website twice a week during the 8-week intervention period and will be followed up continuously for 1 year.

#### Naturalistic Observation Group

Participants in the observation group will only receive regular follow-up at the same visit time point with the MoodBox group and will be followed up continuously for 1 year.

### Outcome Measures and Data Collection Procedure

The follow-up procedure has been summarized in Table 2, including the outcome measures and the assessment time points of the study. Other information includes demographics information, medical history, and current treatment plan, which will be collected by questionnaires via WeChat public account. The adverse events will be assessed by participants' self-report and documented by the research team.

**Table 2 T2:** Measures and visit time point of outcome assessment.

**Visit time point**	**Visit 1 (−7 to 0 days)**	**Visit 2 (day 0)**	**Visit 3 (14 ± 2 days)**	**Visit 4 (28 ± 2 days)**	**Visit 5 (42 ± 2 days)**	**Visit 6 (56 ± 7 days)**	**Visit 7 (84 ± 7 days)**	**Visit 8 (6 months ± 14 days)**	**Visit 9 (9 months ± 14 days)**	**Visit 10 (12 months ± 14 days)**
Informed consent	×									
Patient general demographics	×									
Medical history	×									
Physical and nervous system examination	×									×
DSM-IV diagnosis	×									×
Inclusion and exclusion criteria	×	×								
General information collection form		×	×	×	×	×	×	×	×	×
PHQ-9	×	×	×	×	×	×	×	×	×	×
GAD-7		×	×	×	×	×	×	×	×	×
ASRM		×	×	×	×	×	×	×	×	×
LES		×	×	×	×	×	×	×	×	×
CTQ		×								
IPPA		×								
EMBU		×								
CSQ		×								
Treatment status		×	×	×	×	×	×	×	×	×
Adverse events	×	×	×	×	×	×	×	×	×	×
Adherence to intervention			×	×	×	×				
Satisfaction and acceptability for the intervention			×	×	×	×				

*DSM-IV, Diagnostic and Statistical Manual of Mental Disorders (Fourth Edition); PHQ-9, Patient Health Questionnaire; GAD-7, Generalized Anxiety Disorder-7; ASRM, Altman Self-Rating Mania Scale; LES, Life Event Scale; CTQ, Childhood Trauma Questionnaire; IPPA, Inventory of Parent and Peer Attachment; CSQ, Coping Style Questionnaire*.

#### Primary Outcome

The primary outcome is the efficacy of the intervention measured by the PHQ-9 (22). PHQ-9 is a nine-item reliable and valid self-report depression severity screening and diagnostic tool based on the DSM-IV criteria (23, 24). Response options are “not at all,” “several days,” “more than half the days,” and “nearly every day,” scored as 0, 1, 2, and 3, respectively (total score range from 0 to 27). In the current study, efficacy is defined as the participants score ≥ 2 on less than two items on the PHQ-9 scale at post-treatment assessment. PHQ-9 has demonstrated high reliability and validity in the Chinese population, with Cronbach's alpha for the internal consistency reliability being 0.86, the correlation coefficient for the 2-week test–retest of the total score being 0.86, and positive correlation with the Self-Rating Depression Scale (SDS; *r* = 0.29, *p* < 0.001) and the 36-item Short Form Health Survey (SF-36; correlation coefficients ranged from −0.11 to −0.47, *p* < 0.001) (25).

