### Statistical Consideration

Data management and statistical analysis will be conducted using SAS9.4 (SAS Institute Inc., Cary, NC, USA). The sample characteristics would be compared using chi-square test for categorical variables or using Fisher's Z test when needed; ANOVA tests for normal distributed variables; and Mann–Whitney's U test for non-normal distributed variables. Analysis of efficacy will be based on an intent-to-treat principle, comprising all participants randomized regardless of the treatment group. The Kaplan–Meier survival analysis will be used to calculate the estimated time from baseline to response during 8 weeks' follow-up.

The Cox proportional hazard regression model using the Breslow method will be used to compare estimated time to response between groups, with control for covariates such as age, gender, years of education, and disease-related conditions; also we would use the exact method as sensitive analysis in case of tied survival data. Considering the long interval between visits after week 8, we will also use maximum likelihood estimation for Cox hazard regression model following Shen's work (34) to control left interval truncated data. Secondary analyses will be performed to assess changes from baseline to the endpoint of the study on scores of scales, using mixed-effects model for repeated-measures analysis (MMRM). A *p*-value <0.05 is considered as statistically significant. The Bonferroni method will be used to control multiple comparisons of type I error inflation.

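### The primary outcome is responder status at week 8, but the efficacy comparison given for response is time to response over weeks 0–8, and the sample-size statement mixes the two

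*Protocol article*

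**What the plan says.** - **Outcome (Protocol article, Primary Outcome).** The definition is binary and tied to one assessment: "efficacy is defined as the participants score ≥ 2 on less than two items on the PHQ-9 scale at post-treatment assessment".
- **Timing (Study Design; Table 2).** Participants are "assessed at 2, 4, and 6 weeks after they started to receive the intervention and a post-intervention assessment at 8 weeks". The post-treatment assessment is therefore Visit 6 (day 56 ± 7), and PHQ-9 is also collected at three earlier visits after baseline.
- **Analysis (Statistical Consideration).** Kaplan–Meier "will be used to calculate the estimated time from baseline to response during 8 weeks' follow-up". A Cox model "will be used to compare estimated time to response between groups, with control for covariates such as age, gender, years of education" and disease-related conditions. The other outcome analysis listed is a mixed model on scale scores, described as secondary.
- **Sample size (Sample Size).** The trial is powered on "the proportion of participants without subclinical depression between the MoodBox group with the online psychoeducation group and the observation group in a survival analysis", with a 14% minimum difference after 8 weeks, two-sided alpha 0.025, 80% power, 20% attrition and 145 per group.
- **Persistence (Response Rate).** Sustained response is a secondary outcome. It covers only assessments after week 8 and uses an additional total-score condition.

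**The concern.** A state at week 8 and the time taken to reach that state answer different questions when the state can be entered and left. PHQ-9 is taken at weeks 2, 4, 6 and 8, so a response can be reached and lost before the visit that defines success. The entry rule leaves room for this: a participant with exactly two items scored 2 becomes a responder when one of them falls by a point.

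At stake is what the main p-value means. If the Cox model is read as the test of the primary outcome, a treatment that only speeds up response could be declared effective with no week-8 difference. A treatment that prevents relapse, and so improves week-8 status, could be missed. With the endpoint and the test left in disagreement, the choice between two questions could also be made after the data are seen.

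**Working it through.** **1. The plan's own figure.** The 145 per group corresponds to 145 × 0.8 = 116 evaluable. The control rate is not stated, so I scanned it with the pooled two-proportion formula

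n = [z(0.9875)·√(2p̄(1−p̄)) + z(0.80)·√(p₁(1−p₁) + p₂(1−p₂))]² / 0.14², with p₂ = p₁ + 0.14.

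This gives 116, hence 145, at about 7% vs 21% or 79% vs 93%. A Schoenfeld calculation, with HR = ln(1−p₂)/ln(1−p₁), gives about 145 at 9% vs 23% or 74% vs 88%. So 145 is attainable under either approach. It can be neither confirmed nor called wrong, and it does not reveal which quantity was powered.

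**2. How far the two quantities can differ.** The article gives no response or relapse rates, so all rates here are assumptions. Let r be the probability per visit that a non-responder responds, and q the probability per visit that a responder relapses, over the four visits.

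- Ever responded by week 8: 1 − (1−r)⁴
- Responder at week 8: [r/(r+q)] × [1 − (1−r−q)⁴]

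| r | q | Ever responded | Responder at week 8 | Events no longer responding at week 8 |
|---|---|---|---|---|
| 0.2 | 0 | 59.0% | 59.0% | 0 |
| 0.2 | 0.1 | 59.0% | 50.7% | 8.4 points |
| 0.2 | 0.2 | 59.0% | 43.5% | 15.5 points |
| 0.2 | 0.3 | 59.0% | 37.5% | 21.5 points |

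For example, with r = 0.2 and q = 0.1: 1 − 0.8⁴ = 0.590, and (0.2/0.3) × (1 − 0.7⁴) = 0.507.

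**3. Whether the two tests can disagree.** I simulated 116 per arm at two-sided alpha 0.025, 5,000 trials per scenario, with an unadjusted log-rank test on first response against a two-proportion test at week 8.

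- *Same week-8 status, different speed.* With r = 0.3, q = 0.272 against r = 0.2, q = 0.1, both arms have about 50.7% responders at week 8. The first-response hazard ratio is ln(0.7)/ln(0.8) = 1.60. The log-rank test is significant in about 75% of trials (76% by Schoenfeld's formula) and the week-8 test in about 2%.
- *Same speed, different week-8 status.* With r = 0.2 in both arms and q = 0.1 against 0.3, week-8 response is 50.7% against 37.5%, a difference of 13.2 points. The log-rank test rejects at about its nominal 2.5% and the week-8 test in about 42%.

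These scenarios were built to separate the two quantities. They show that disagreement is possible in both directions, not how large it will be in this trial.

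**4. What a week-8 comparison would need.** Using the formula in step 1 with the stated alpha, power, difference and attrition:

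| Assumed control rate | n per group | Power with 116 evaluable |
|---|---|---|
| 7% | 145 | 80% |
| 20% | 238 | 56% |
| 40% | 302 | 46% |
| 60% | 268 | 51% |
| 79% | 145 | 80% |

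**The case against.** **No text says that relapsed participants count as successes.** A reader might infer this, but the word first does not appear and the Cox event is not separately defined. It follows from the usual reading of time to response when no persistence rule is given, and the effect vanishes if nobody relapses before week 8. This stands, so the point about relapse is conditional.

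**The Cox model is not labelled primary.** A reader might take it to be so, because Sample Size links the primary outcome to a survival analysis and no other between-group test of response is given. That inference is reasonable but is not in the text. The absence of a week-8 test would not be a finding by itself, since an unseen analysis plan could supply one. What remains is that the stated sections disagree, and an added test would not remove that.

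**Survival may be what was intended.** Sample Size and Statistical Consideration both point that way, and a Kaplan–Meier curve read at week 8 yields a cumulative proportion. The loosely worded section could be Primary Outcome. This also stands: keeping the survival analysis with a redefined endpoint is a valid repair.

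**The size is uncertain.** The one stability figure in the article, a 2-week test–retest correlation of 0.86, concerns the PHQ-9 total score and suggests good short-term stability. It is an imperfect guide to the item-count rule, but it gives no ground for assuming frequent relapse. The simulation also omits the planned covariate adjustment. In some scenarios time to response has the greater power, so the defect is the mismatch of question and not a loss of power as such.

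**Conclusion.** The concern holds as an inconsistency in the stated text. The primary outcome is a week-8 state, the between-group analysis given for response is time to response over weeks 0–8, and the sample-size statement combines the two. Followed as written, the plan could yield a main p-value that does not test the stated primary outcome.

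The size cannot be fixed from the article. Under the assumed rates (response 0.2 per visit, relapse 0.1 to 0.3), between 8.4 and 21.5 points of the 59% who ever respond would not be responders at week 8. With no relapse that component is zero, although the Cox model would still compare speed rather than week-8 status. The documents do not support the stronger claims that the plan definitely counts relapsed participants as successes, or that it will declare efficacy wrongly at any particular rate.

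It should be settled before analysis, because it determines what the primary result means.

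**What to change.** Make Primary Outcome, Statistical Consideration and Sample Size refer to one quantity.

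**Preferred, because it matches the stated outcome.** Under Statistical Consideration, make the primary analysis a covariate-adjusted comparison of Visit 6 responder proportions. Report it as a risk difference with confidence interval for MoodBox against each comparator, at two-sided alpha 0.025. Keep Kaplan–Meier and Cox time to response as secondary. Base Sample Size on the week-8 proportion and state its assumed control rate.

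**Alternative, if time to response is what was meant.** Redefine the primary outcome accordingly, with an explicit event definition and a rule for relapse before week 8. Report the week-8 responder proportion as a key secondary outcome, and state the control rate or hazard ratio behind the 14%.

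**Cost.** Wording only, since PHQ-9 is already collected at Visit 6. The downside is that the power claimed for 145 per group may have to be restated: for the week-8 comparison it ranges from about 46% to 80% over the assumed control rates tabulated above, and in some scenarios it is lower than for time to response.
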